### ***Methodological integrity***

The study adheres to ethical guidelines as outlined by the University of West of England as well as the British Psychological Society. The CI is a Chartered Counselling Psychologist with many years of clinical and research experience in the field of mental health. She has been working with people with MS in a research context systematically since 2017. She has been interviewing participants adhering to qualitative methodology and principles and has been the main administrator of quantitative questionnaires. She is thus competent and experienced to design and conduct the current mixed method pilot project. She has been keeping a research journal where all processes are outlined in order to achieve transparency in the final report. The study processes have been reviewed by the supervisor and collaborators of the project and it has been thoroughly discussed in the PPI group where no major amendments were recommended. The analysis of the data will be discussed in the group of researchers and an experienced qualitative researcher external to the project will audit the analysis of the qualitative data to ensure integrity and trustworthiness.

### **Stages of research/ Timetable**

|                                                                                               |                                                                                                                                                                                                                                      |
|-----------------------------------------------------------------------------------------------|--------------------------------------------------------------------------------------------------------------------------------------------------------------------------------------------------------------------------------------|
| Preparation and discussion in PPI group

February 2022                                  | The PPI group has been formed through the Research Network of the UK MS Society                                                                                                                                                      |
| Finalise and submit IRAS application and FREC ethics application

February - March 2022 | The final IRAS application will be submitted as soon as final approvals are received in the research team.

Following IRAS approval, all forms and approval letter will be forwarded to UWE Faculty Research Ethics Committee. |

|                                                                                                                                                         |                                                                                                                                                                              |
|---------------------------------------------------------------------------------------------------------------------------------------------------------|------------------------------------------------------------------------------------------------------------------------------------------------------------------------------|
| 
Meeting with the team of professionals at the Bristol and Avon Multiple Sclerosis Centre
 
Initiating recruitment stage
 
October 2022
 | 
The study processes and interventions will be presented to the team of professionals at BAMS centre and initial meetings with potential participants will take place.
 |
| 
Baseline collection of data and commencement of intervention
 
–November 2022
                                                               | 
The baseline collection of quantitative and qualitative data will take place before commencement of the intervention.
                                                 |
| 
Implementation of intervention
 
November 2022 – January 2023
                                                                               | 
Intervention will be implemented for 8 weeks after commencement. Participants will attend 8 weekly sessions which will last 1 ½ hours each.
                           |
| 
End of intervention collection of data.
 
February 2023
                                                                                     | 
The end of intervention collection of quantitative and qualitative data will take place
                                                                               |
| 
One month follow up collection of quantitative data
 
March 2023
                                                                            | 
One – month follow up collection of quantitative data will take place.
                                                                                                |
| 
Three – month follow up collection of data
 
June 2023
                                                                                      | 
Three – month follow up collection of quantitative and qualitative data will take place.
                                                                              |
| 
Data analysis and preliminary findings
                                                                                                           | 
Qualitative and quantitative data will be analysed in this period
                                                                                                     |

|                                                                                                  |                                                                                               |
|--------------------------------------------------------------------------------------------------|-----------------------------------------------------------------------------------------------|
| July – September 2023                                                                            |                                                                                               |
| Writing up of internal report for VC – ECR Award (funder) and publications

September 2023 | Final report and articles for publication will be written.                                    |
| Dissemination of findings

August – December 2023                                          | In the same period dissemination of findings and dissemination strategies will be implemented |

### **End of the study**

The study will end when the three – month follow – up data will be collected by all participants. These will include the questionnaires completion and the qualitative interviews with the lead researcher. This is estimated to take place in June 2023.

### ***Patient involvement statement***

#### ***PPI involvement in the design***

Five members of the Research Network of UK MS Society agreed and participated in a focus group with the project Chief Investigator (CI) ([name]) to discuss intervention implementation and research design. They were sent a brief overview of the research project and MyMS-Ally intervention structure. The CI also presented the intervention and the study processes briefly in the beginning of the group before moving on to the discussion. The focus group was semi – structured with specific questions that had been developed by the CI and focused on: a. intervention, b. research processes, c. dissemination. The CI also encouraged open discussion on any feedback or input members might have had on the intervention and research plan. The members’ feedback is summarised below and incorporated in the intervention planning and research design:

1. PPI group members provided substantial feedback on intervention structure and delivery:
  - The intervention sessions should be timed so participants are aware how much time will be spent on each theme in the session. This is to ensure that there will be enough time without overburdening the participants.
  - They agreed that the intervention should be conducted online as it is easier for people with MS with complex needs to participate from the comfort of their

homes. It is also easier for them as they will not have to travel and it makes it easier to concentrate and tackle issues of fatigue.

- Intervention (and data collection processes) should be scheduled for a time in the day when it's most appropriate for people with MS, therefore avoid late afternoon and evening.
  - There needs to be flexibility with attendance; even though we want participants to be committed to the intervention we should also respect issues of fatigue that might come up or "bad days" and allow people to continue to participate even if they miss a session.
  - There needs to be "feedback" in the form of reminders or overview of the sessions at the end, between or in the beginning of the next session where participants will be able to remind themselves of the main themes and incidents discussed in the sessions. This will accommodate any cognitive difficulties they might experience.
2. PPI group members stated that the initial plan for 6 – 12 participants for one group will not be effective as more than 5 or 6 members in a group makes it very difficult to interact and have in – depth interactions. They strongly suggested recruiting 5 – 6 participants and if more people expressed interest in taking part then more than one groups will be offered.
  3. PPI group members agreed with the sampling inclusion and exclusion criteria and highlighted areas that the research team must be mindful of as they recruit participants:
    - They suggested we do not include an upper age limit as people who are 70 years old might be more than capable and willing to share in a group which will be beneficial for the rest of the participants. Therefore, the research team changed the criterion to people above 18 without an upper age limit.
    - Researchers should consider the impact of age of participants in the group intervention.
    - Researchers should consider the impact of physical disability in the group intervention.
    - PPI group agreed that the intervention should be conducted online and therefore participants should have access to a device (computer, laptop, tablet, phone) and to the platform intervention and research data collections processes will take place on (Microsoft Teams).
  4. There needs to be flexibility with data collection processes. There need to be breaks, time for rest at the time of interviews, perhaps stop an interview and go back to the participant when they are ready to continue. Moreover, there needs to be flexibility with completing questionnaires so there might be a need for the CI to administer the questionnaires verbally, online or over the phone.
  5. If a participant has difficulty articulating themselves or completing questionnaires, it is sometimes useful to have a carer with them to help so this will be allowed in data collection processes.

6. In online delivery of the intervention and data collection, captions must be on in Microsoft Teams.
7. The members suggested the following organisations along with the NHS that would benefit to be involved in the dissemination of the study findings and the intervention:
  - UK MS Society
  - MS Trust
  - Shift MS
  - Overcoming MS

They also suggested podcasts as an efficient dissemination strategy. All the above will be implemented in the dissemination of the research conclusions.

8. No major amendments were suggested in the risk and benefits part of the design. The members agreed with the suggested risks and benefits. Their recommendation was to ensure that the benefit of participants experiencing the benefits of the intervention in their experience and management of MS should be first in the list.
9. For future steps of this project, the members suggested that the research team should enhance inclusion by recruiting from organisations across the country (given that the intervention and evaluation study processes will be implemented online) as well as receiving funding to incorporate means and software that will help more people with MS with complex needs and physical difficulties to take part in the intervention and future evaluation studies.
10. Three of the five members of the PPI focus group requested to stay updated and involved in the project. Following their request, the CI will arrange group meetings with them at the important milestones of the research project and their involvement will be further discussed.

## **Methods of Analysis**

### ***Qualitative Data***

The collection, analysis and final presentation of findings of the qualitative data will draw on guidelines of Interpretative Phenomenological Analysis (Smith et al., 2022). The analysis will be thorough and detailed, and every participant's interviews will be analysed separately in a case-by-case series. The Chief Investigator will first listen to the recording and read each transcript in order to gain familiarity with each case and make first observations, noting linguistic, descriptive, and conceptual codes throughout the transcripts. A longitudinal analysis will be conducted for each case conveying the diachronic developmental dimension in terms of their experience of the intervention and the impact on the experience and management of their Multiple Sclerosis. A case-by-case analysis and a careful and exhaustive examination across cases will be conducted to reveal the divergences and commonalities amongst the cases. The focus will be on the subjective experience of the MyMS-Ally psychological intervention and how participants appraise, perceive the intervention helpful or unhelpful, any change processes they might experience in relation to intervention processes. Analysis will be cyclical and iterative, constantly going back and forth in the data engaging in a dialogue. Emerging themes will be grouped in tables and diagrams and discussed in the research team, who will review all the steps of the analysis. Engaging in a more interpretative level of analysis, the meaning of each theme will be discussed as grounded on the participants' narratives. Following completion of the qualitative analysis, an experienced qualitative researcher, external to the research team, will audit the analysis and the final themes.

### **Quantitative Data**

Descriptive statistics (means and standard deviations) will be calculated to provide insight into the participants' characteristics as well as indication of any potential changes in the mean scores between the different administration of the measures at four different points in time

(baseline, end of intervention, 1 month and 3 month follow up). Within subjects effects will also be calculated and reported. The final quantitative findings will be presented in a table reporting F, df, effect sizes, CI and p values.

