The recent literature focuses mainly on generic models of psychological interventions which cannot cover the complexity and the unpredictability of MS. However, given recent developments of process – based psychological interventions, psychological approaches can be formulated based upon the specific characteristics of the disease for people with MS. The people with MS' voices and preferences can guide psychological intervention programmes development as well as methods of evaluation of these programmes. The current research

project aims to address the above issues, following from a longitudinal, exploratory, mixed method study on the experience of psychosocial interventions for 20 people with MS ([name], Anagnostopoulos & Triliva, 2021). Results of this study revealed the interplay between MS and psychosocial interventions and the journey of the participants from the despair at diagnosis, helplessness and punishment to the new preferred identity that encompasses the MS body, empowerment and forgiveness. The themes of the study guided the development of the novel group psychological intervention MyMS-Ally and the current research project explores the feasibility and acceptability of this intervention programme.

The primary objective of the current study is the investigation of the feasibility and acceptability of the novel group psychological intervention MyMS-Ally. As a secondary objective, the researchers will collect primary data to evaluate the effects of the intervention on quality of life, depression, anxiety and emotion regulation. A mixed method design will be implemented. Qualitative individual interviews will provide insight into the participants' experiences taking part in the intervention, how they perceive the impact on their experience and management of MS and which intervention processes they perceived as helpful or unhelpful. Quantitative outcome measures will record any potential change. The aim of the study is to reach conclusions with regards to the relevance and appraisals of participants taking part in the intervention so that final modifications are made and the intervention can be further evaluated. Additionally, the study aims to reach statistically significant results that will indicate the impact of the intervention but also to indicate effects that are meaningful in everyday work with people with MS (Kazdin, 1999).

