Those who will agree to participate will be asked to provide the CI with their demographics, email and telephone contact details in order to commence with the data collection process as well as to inform them of the start of the group intervention. Only the CI will have access to the participants' personal details. Five to six participants will be recruited and allocated to one group which will last two months (eight weekly sessions) following PPI involvement input. If more people with MS show interest in participating in the study, then more than one groups will be offered.

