## **Participants**

Recruitment and implementation of the intervention will take place in the Bristol and Avon Multiple Sclerosis Centre in Southmead Hospital, Bristol. A group of 5 - 6 participants will be recruited to take part in the MyMS-Ally group intervention. The group size reflects the minimum number of members of a group psychological intervention for meaningful interactions to be unfolded and the maximum number which allows enough time and space for each member to use the group effectively (Saracutu et al., 2018). The size of the sample also reflect the recommendations made in the PPI involvement focus group. Should more people with MS express interest in taking part, more than one groups will be offered. Eligible participants will be aged 18 years or above, diagnosed with multiple sclerosis more than two years ago, able to read, write and speak English and able to engage into eight weekly group psychological intervention sessions (2 months). The group intervention as well as data collection processes will take place online therefore access to the internet and to a device where they can use Microsoft Teams software on are required. People with MS with suspected and/or diagnosed comorbidity with Depression, Bipolar Disorder or Psychotic Disorders will not be able to participate in the study.

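### With one therapy group and no comparator, the planned F, CI and p-values describe change among these members and cannot show the impact of MyMS-Ally

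*Protocol*

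**What the plan says.** Under Methods of Analysis, Quantitative Data, the protocol plans means and standard deviations at four time points (baseline, end of intervention, one month and three months). It then adds: "Within subjects effects will also be calculated and reported". The reporting format follows: "The final quantitative findings will be presented in a table reporting F, df, effect sizes, CI and p values". No group, facilitator or cluster term is named.

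The base design is a single group, stated at the end of the eligibility text: "Five to six participants will be recruited and allocated to one group which will last two months (eight weekly sessions". More groups are only a possibility, and their number is not fixed: "Should more people with MS express interest in taking part, more than one groups will be offered". Conflict of interest and Risks for researchers both describe one facilitator. No comparison arm appears anywhere.

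The Participants section explains the size of the group by interaction between members: it is "the minimum number of members of a group psychological intervention for meaningful interactions to be unfolded", and also the largest number that leaves each member enough time and space.

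On what the numbers are for, Secondary objectives calls the outcome data preliminary. Purpose and design goes further: "the study aims to reach statistically significant results that will indicate the impact of the intervention". Research design and methodology likewise presents the mixed-method design as a basis for statistically significant conclusions.

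**The concern.** A within-subjects F compares the mean change over time with how much members differ from one another in their changes. What all members share does not enter that comparison's error term. Here they share a facilitator, the sessions and each other, and interaction between them is part of how the intervention is meant to work. They also share calendar time, and there is no untreated group to show what would have happened without the sessions.

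If the group happens to go well or badly, or if scores drift or regress toward the mean, the time effect moves and the error term does not. A small p-value is then read, under Purpose and design, as a sign that MyMS-Ally works. The Scientific justification section says the study should inform the design of the later evaluation study. Effect sizes and intervals passed on as intervention-level estimates would look more precise than they are and would give that design no warning to allow for clustering.

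**Working it through.** **Figure to reproduce.** None. The protocol states no power, significance level, effect size, SD or ICC.

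**Inputs from the protocol.** Members per group m = 5 or 6; groups K = 1 in the base plan; 4 time points; no comparator.

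**Assumed.** ICC of change within a therapy group, ρ, from 0 to 0.20; two-sided 5% level; true mean change across groups zero; sphericity of the person-level errors.

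**Step 1: can the group effect be separated from time?** Between-group degrees of freedom are K − 1 = 0. The group and facilitator component cannot be estimated, and no model can remove it from the time effect. The same holds for a natural time trend and regression to the mean, because there is no comparator.

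**Step 2: interval for baseline-to-end change, inference beyond the group.** With the variance of an individual change set to 1:
- true variance of the mean change = [1 + (m − 1)ρ]/m
- expected value of the usual estimate = (1 − ρ)/m
- ratio of true to estimated SE = √{[1 + (m − 1)ρ]/(1 − ρ)}

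For m = 6:
- ρ = 0.01: √(1.05/0.99) = 1.03
- ρ = 0.05: √(1.25/0.95) = 1.15
- ρ = 0.10: √(1.50/0.90) = 1.29
- ρ = 0.20: √(2.00/0.80) = 1.58

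Under normality the coverage is exact: the probability that a t variable with m − 1 df lies within ± (critical value ÷ ratio). With 5 df the critical value is 2.571. The limits become 2.496, 2.241, 1.991 and 1.626, and coverage is 94.5%, 92.5%, 89.7% and 83.5%. At ρ = 0 it is 95%. For m = 5 at ρ = 0.05, 0.10 and 0.20 it is 93.1%, 91.0% and 86.2%.

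**Step 3: the four-time-point F test, by simulation** (one group, no average effect, 200,000 replicates per cell). The persistent version has a group shift that is zero at baseline and constant afterwards, with variance 2ρ/(1 − ρ) against unit residual variance. The free version draws an independent group deviation at each time point.

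| ρ | m = 6, persistent | m = 6, free | m = 5, persistent | m = 5, free |
|---|---|---|---|---|
| 0 | 5% | 5% | 5% | 5% |
| 0.01 | 5.4% | 5.8% | 5.3% | 5.6% |
| 0.05 | 7.4% | 9.9% | 6.9% | 8.8% |
| 0.10 | 10.4% | 16.1% | 9.2% | 13.7% |
| 0.20 | 17.5% | 30.6% | 15.0% | 25.2% |

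Degrees of freedom are 3 and 15 for m = 6, and 3 and 12 for m = 5.

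**Step 4: if more groups run.** With two or three groups of six and no group term the rates are similar: about 10% at ρ = 0.05 in the free version. A test on group means holds 5% but has K − 1 df: the critical t is 12.71 for two groups (2.20 at person level with 12 people) and 4.30 for three (2.11 with 18). At ρ = 0.05 the mean half-width of the interval is 4.7 residual SDs against 0.89 for two groups, about five times wider, and 1.45 against 0.71 for three.

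These figures cover clustering only. Time trend and regression to the mean come on top, and the protocol gives nothing from which to size them.

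**The case against.** The protocol never says that observations are independent and names no model. If several groups run, an analysis plan that is not shown could add a group term. That stands: a reader might infer that the protocol fixes a wrong multi-group analysis, but the text does not support it. It does not help the one-group base plan, where no term can be fitted.

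A reader might also infer that the intervals are simply too narrow. They are too narrow only for inference beyond the group studied, and only if the ICC is above 0. At 0.01 the loss is negligible. For change in these particular members they are not too narrow on this ground, and Research design and methodology does describe an idiographic aim. But the same section and Purpose and design also seek significant conclusions, in the latter case about the intervention.

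It is tempting to say that the number of independent units is the number of groups. That is literally true only at an ICC of 1. At 0.05 with groups of six the design effect is 1 + 5 × 0.05 = 1.25, so 12 people carry the information of 12/1.25 = 9.6. Few groups limit the degrees of freedom for estimating between-group variation, which is a different matter.

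Nor is clustering the only obstacle: at ICC 0 the lack of a comparator would still stop the p-value from showing an effect of MyMS-Ally.

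Last, the stakes are modest. Feasibility and acceptability are primary and are studied mainly through interviews; the questionnaires are secondary. This limits the remedy to wording but does not make the stated claim correct.

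**Conclusion.** The point holds for what the protocol fixes: one group, one facilitator, no comparator, a table of F and p-values, and the aim that significance should indicate impact. The first four cannot deliver the fifth, and no analysis plan can change that with one group. This conclusion does not depend on any ICC.

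The size does. If results are carried beyond the group, the nominal 5% F test reaches twice its level at an ICC of about 0.10 under a persistent group effect, and at about 0.05 under a freely varying one (groups of six). All ICCs are assumptions. If several groups run, the point is weaker, because the analysis is then open to repair, though only on one or two degrees of freedom with two or three groups. A facilitator common to all groups would still be inseparable from time.

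**What to change.** In Methods of Analysis, Quantitative Data: report means, SDs and individual trajectories, by group if more than one runs. Label any CI or effect size as conditional on the group(s) and facilitator studied and as uncontrolled for time trends. Give no p-value as evidence of the intervention's impact.

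In Purpose and design and in Research design and methodology: remove the aim of statistically significant results or conclusions about impact.

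If several groups run: record group membership, and state that person-level intervals leave out between-group variation. A group-level test on one or two degrees of freedom should not be required, since its interval would be close to uninformative.

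The cost is a few sentences and no new data. The secondary outcomes lose an inferential p-value, but the protocol states no power that would be given up, and individual trajectories suit its idiographic aim.
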